##### Dual-task function (Aim 2):

We measure function using validated clinical tests, performed in a clinical space in an area that is distraction free. The *Timed Up-and-Go test (TUG)* is a timed test of a person’s ability to stand from a chair, walk 10 feet (3 m), turn around, and return to sitting (60). Presence of CIN has been associated with longer TUG times (61–64). To measure dual-task function, we use the TUG performed simultaneously with a cognitive task consisting of audibly counting backward by subtracting 3 from a given number (*TUG-Cog*). We previously reported that BC survivors with CIN demonstrated dual-task functional deficits with up to 78% demonstrating increased risk of falling as measured by TUG-Cog (17).

#### Secondary and tertiary outcome measures

##### Patient-reported outcome (PRO) survey instruments for measuring symptomatology:

Patient self-report surveys data are collected as described in the *Primary Outcome Measures, Sensation* section above. In addition to the primary PRO-based outcome measure, we collect the following PRO measures:

###### CIN symptoms of temperature.

Self-reported sensations of “hotness” or “coldness” in the last 7 days are collected via a validated 11-point Likert scale (59).

###### European Organization for Research and Treatment of Cancer’s Quality of Life Questionnaire, Chemotherapy-Induced Peripheral Neuropathy (CIPN-20):

is a validated 20-item patient reported questionnaire instrument for longitudinal evaluation of neuropathy symptoms induced by chemotherapy for a recall period of “during the past week” (65).

###### Other symptoms.

Using the Patient-Reported Outcome version of the Common Terminology Criteria for Adverse Events (PRO-CTCAE) items 39 through 56, cancer-related symptoms such as balance problems, nausea or vomiting, dizziness, sensitivity to light or noise, feeling like “in a fog”, confusion, sadness, and anxiety can be queried for the recall period of the past 7 days (66).

*The Brief Pain Inventory (BPI)* is validated to elicit momentary (“right now”) and retrospective (prior 24 h period) self-reported pain and relevant functional capacity (67).

*The Brief Fatigue Inventory (BFI)* is validated to elicit momentary (“right now”) and retrospective (prior 24 h period) self-reported fatigue and relevant functional capacity (68).

*The Short Form Health Survey (SF-36)* is a quality of life (QOL) measure in cancer survivorship validated to elicit momentary and retrospective (last 4 weeks) assessment of an individuals health status. One report identified this survey as a predictive tool for assessing fall risk amongst cancer survivors (69).

*The Generalized Anxiety Disorder 2-Item (GAD-2)* is a validated assessment of retrospective (last 2 weeks) self-reported anxiety (70).

*The Patient Health Questionnaire-2 (PHQ-2)* is a validated assessment of retrospective (last 2 weeks) self-reported depression (Li et al., 2007).

###### Ecological momentary assessment (EMA).

EMA is a method of experience sampling that captures an individual’s self-report of their symptoms “right now” (72). We modified self-report assessments as needed to elicit self-report of symptoms “right now” at the beginning and end of intervention sessions as well as remotely through the MyCap phone application. Toward this end we used EMA items from the BPI and BFI and created EMA versions of these surveys: 11-pt Likert scale assessment of numbness and tingling in the extremities, 11-pt Likert scale of hotness and coldness in the extremities and the EORTC CIPN-20. Rather than modifying the PRO-CTCAE items 39 to 56, we used the Sports Concussion Assessment Tool symptom EMA survey of physical, cognitive, and emotional symptoms of mild brain injury which align with PRO-CTCAE items 39 to 56.

###### Assessment during the activity just performed:

Finally, to query whether symptomatology was affected by the interventional activity, we modified all PRO instruments to query for the recall period of “during the activity just performed”.

*Satisfaction with intervention* is measured after each class using a 7pt Likert scale and prompt for feedback about what did/did not work per class. Feedback is used to improve future sessions.

*The Intrinsic Motivation Inventory (IMI)* was developed from the perspective of Self Determination Theory to assess 7 dimensions of experience: Interest/Enjoyment, Perceived Competence, Effort/Importance, Pressure/Tension, and Choice (73). We administer the 9-item short form of the IMI monthly to optimize instruction around low Pressure/Tension and high Interest/Enjoyment (56,57) as well as to explore relationships between adherence, motor effects, and IMI dimensions including perceived benefit (i.e., Effort/Importance).

##### Function

###### Activity tracking:

Participants are asked if they have participated in the following activities: physical therapy, occupational therapy, fitness activity, other therapeutic or fitness activities. If any category of activity is checked as having occurred then participants are prompted to estimate the amount of time spent doing the activity since we last saw them (hours, minutes). If participants indicate that physical or occupational therapy were started during the study period, we remind them that these are an exclusion criterion and give them the choice of postponing engagement in skilled therapy until after completion of the study or termination of study participation.

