**Discussion:**

The scientific premise of this study is that Tango stands to improve CIN symptoms significantly more than the current standard of care by combining PA with auditory-motor entrainment and social engagement. Our findings may lead to a safe non-pharmacologic intervention that improves CIN-related deficits.

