### Eligibility criteria

The eligibility criteria of this study follows the criteria described in Lantis et al. (2023) (46). Briefly, participants are eligible for this study if they are 40 years old or older, diagnosed with BC (all stages), experiencing CIN (European Organization for Research and Treatment of Cancer, Chemotherapy-Induced Peripheral Neuropathy outcome measure (CIPN-20) sensorimotor score > 1 or similar on an equivalent measure), finished with taxane-based chemotherapy treatment for at least 3 months, able to understand and comply with directions associated with testing and study treatments, and if they demonstrate postural control measurements outside of normative values (47). Participants are excluded from the study if they meet any of the following criteria: pre-existing vestibular disorders, history of motor deficits or neurological disease other than CIN-related, poorly controlled diabetes (HbA1c ≥ 8.0), non-ambulatory or lower extremity amputation (Note: assistive devices allowed), participating in physical or occupational therapy during the study (Note: engagement in additional therapies or physical activities (e.g. acupuncture) will be documented), or contraindicated to participate in unsupervised activity due to other issues (e.g. herniated vertebral disc).

We expect the study population to be representative of the demographics of the BC survivorship population in the United States between both sites. The CDC reports that 99% of BC cases occur among women and only 1% among men. The CDC census reports the rate of new BC cases in 2019 per 100,000 women by race as White/non-Hispanic 132.5, Black/non-Hispanic 128.4, American Indian and Alaska native/non-Hispanic 101.7, Asian and Pacific Islander/non-Hispanic 104.5, and Hispanic 101.9 (48).

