#### Control intervention with optional 1-way crossover: SOC with EXP

The active control intervention consists of 4 weeks of SOC, as prescribed by each participant’s medical oncologist. Within SOC, medical oncologists may prescribe pharmacologic treatments such as tricyclic antidepressants, anticonvulsants, and serotonin-norepinephrine uptake prohibitors (6,8,58). They may also recommend exercise and/or physical therapy (6). During the 4 weeks, clients are asked, weekly, to document their numbness/tingling due to CIN and any adverse events that occur via a smart phone application (i.e. the MyCap version of REDCap). After completion of outcomes assessments at the primary endpoint of 4 weeks, individuals in the CON arm will have the opportunity to cross over immediately to participate in the EXP tango intervention.

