### Statistical analysis

All outcome analyses will be performed on an intent-to-treat basis, and all hypothesis tests will be two-sided and at the 5% significance level or 95% confidence level. Longitudinal linear mixed models will be used to model changes in PROs and dual-task function. Fixed effects will be included for condition, session number within condition, baseline outcome measure, age, diabetes status, physical fitness activity (defined by weekly duration and metabolic equivalents), and number of previous chemotherapy lines. Random effects for subjects and study center will be used to account for within-subject and within-center correlation, and covariance estimated by restricted maximum likelihood. Exploratory Aim 3 will be assessed via causal mediation analysis using marginal structural models. The primary estimand will be the contrast representing the difference in mean change in outcome measure from baseline to week 4 (end of randomized treatment comparison) between treatment groups.

While we expect balance between groups due to randomization, we will adjust for potential confounders including age, body mass index, concurrent medications, and other variables if an imbalance between groups occurs by chance. Pearson’s *R* will be calculated to correlate PROs, functional outcomes, biomechanical outcomes, brain activity, and biomarker outcomes. We use a longitudinal mixed effect model to analyze all outcomes and do not impute missing outcomes. Subjects will be analyzed in the group to which they were randomized regardless of compliance with the assigned intervention. We will evaluate the effect of the number of intervention sessions completed on outcomes.

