## Discussion

As BC survival rates improve due to available treatments such as chemotherapy, the long-term quality of life for survivors has become a crticial focus of care. The rationale for this study stems from accumulating evidence that PA represents a viable non-pharmacologic avenue to treat one debilitating symptom of survivorship: chronic CIN (6, 17, 25). As a candidate form of neurologic dance training, Tango has been demonstrated to improve quality of life in populations with neuropathology (38, 46, 54). The scientific premise of this study is that Tango stands to achieve more gains than the current medical SOC for CIN by combining PA with rhythmic musical engagement and delivering the intervention in a socially-engaged environment. Based on previous data establishing safety, feasibility, and initial effect of Tango for survivors with CIN (38, 46), we have designed a randomized controlled trial to compare the effectiveness of the SOC versus an experimental arm that delivers Tango. We assess comparative effectiveness in terms of patient-reported, functional, and neurophysiologic outcomes relevant to BC survivorship. Our findings may lead to a safe, effective, simple, economical, non-pharmacologic intervention that improves CIN-related deficits and symptoms through activity that can be performed with a friend or loved one. Adding small doses of NDT as standard of care (SOC) for survivors with CIN is a simple, cost-effective solution that can be implemented anywhere in the world without major regulatory hurdles. Better functional recovery for survivors with CIN will lead to improved quality of life, short-term, and long-term health and wellness outcomes for these individuals. Therefore, the risks that participants in this study might incur are minor relative to the potential benefits of improving symptoms and function for BC survivors with CIN and measurable balance deficits.

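### The comparator delivered is standard of care without physical or occupational therapy, although it is labelled plain standard of care; the rule for those who start such therapy can also cost the week-4 TUG-Cog value

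*Protocol article*

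**What the plan says.** All references are to the protocol article.

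- **What SOC contains.** Under Control intervention with optional 1-way crossover, the control is four weeks of SOC as each participant's oncologist prescribes it. Drugs are listed, and then: "They may also recommend exercise and/or physical therapy (6" (the quote breaks off at a reference number).
- **The bar.** Eligibility criteria exclude anyone "participating in physical or occupational therapy during the study", with no distinction by arm. Other co-interventions are treated differently: "engagement in additional therapies or physical activities (e.g. acupuncture) will be documented".
- **What happens if PT/OT starts.** Under Activity tracking, participants are reminded of the exclusion, and staff "give them the choice of postponing engagement in skilled therapy until after completion of the study or termination of study participation".
- **How the comparison is labelled.** Study Design calls the comparator usual care. The abstract's premise is that "Tango stands to improve CIN symptoms significantly more than the current standard of care". The Discussion says that the trial will "compare the effectiveness of the SOC versus an experimental arm that delivers Tango".
- **Analysis.** Statistical analysis plans a mixed model without imputation, with participants kept in their randomised group whatever their compliance. On covariates: "Fixed effects will be included for condition, session number within condition, baseline outcome measure, age, diabetes status", among others. The primary contrast is at week 4.

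**The concern.** There are two separate issues.

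First, the definition of SOC and the bar on PT/OT cannot both hold in full. Participants are selected for abnormal postural control, and physical therapy is one of the few named parts of SOC that plausibly bears on function, the subject of Aim 2. With it removed, the trial compares Tango with SOC without PT/OT. A conclusion that Tango beats SOC would be broader than the comparison made.

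Second, the Activity tracking rule ties a co-intervention to leaving the study. Someone who needs PT/OT soon after randomisation, and prefers it to staying, leaves before the primary endpoint. Such a person may be functioning worse than the baseline data predict, so the loss may be informative. It is also avoidable, because the week-4 visit already exists.

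**Working it through.** **Side-by-side reading**

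1. SOC may include physical therapy (Control intervention section). PT/OT is excluded for everyone (Eligibility criteria) and the exclusion is applied after enrolment (Activity tracking). The control delivered is therefore SOC minus PT/OT. Drugs, exercise and other therapies remain.
2. The rule operates before week 4: Table 3 tracks outside activity at Tango sessions and weekly during SOC.
3. Tables 1 and 2 schedule TUG-Cog at baseline and week 4, with nothing between. A participant whose participation ends before week 4 would have no post-baseline value for the Aim 2 primary outcome. The numbness and tingling score is partly covered by the weekly SOC reports and the session reports in Table 3.
4. Postponement until after study completion means at least week 12 in the Tango arm (Table 1). For controls who take up the optional crossover it means at least week 16 (Table 2). The article does not say how long it lasts for a control who declines Tango.

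**The plan's own figures**

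From Power calculations: 70 enrolled and 50 retained per arm (read as 140 in total, as that section states), two-sided 5%, d = 0.56 for Aim 2.

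- Aim 2 power = Φ(0.56 × √(50/2) − 1.96) = Φ(0.84) = 80.0% (79.2% with the t distribution).
- Aim 1: SD = √((2.5² + 1.9²)/2) = 2.220; power = Φ((1.25/2.220) × 5 − 1.96) = 80.4% (79.6% with t).

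The stated 80% is reproduced for both outcomes. Planned losses per arm are 70 − 50 = 20.

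**Size of the follow-up loss**

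The documents give no rate of starting PT/OT, no exit rate and no baseline correlation for TUG-Cog. The inputs below are assumptions.

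- p, the share of one arm leaving before week 4 because of PT/OT: 0.02 to 0.10, which is 0.02 × 70 = 1.4 to 0.10 × 70 = 7 people.
- g, the difference between leavers and stayers beyond what the model explains: 0.25 to 0.5 residual SD.
- ρ, the correlation of baseline with week-4 TUG-Cog: 0.5 to 0.8.

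The mean among stayers differs from the whole-arm mean by p × g residual SDs, and one residual SD is √(1 − ρ²) outcome SDs. So shift = p × g × √(1 − ρ²).

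- Low: 0.02 × 0.25 × √(1 − 0.8²) = 0.02 × 0.25 × 0.60 = 0.003 SD.
- High: 0.10 × 0.5 × √(1 − 0.5²) = 0.10 × 0.5 × 0.866 = 0.043 SD.
- Against the target, reading d = 0.56 on the same SD scale: 0.003/0.56 = 0.5%; 0.043/0.56 = 7.7%.
- Against the adjusted standard error √(2/50) × √(1 − ρ²), which is 0.12 at ρ = 0.8 and 0.173 at ρ = 0.5: 0.003/0.12 = 0.025; 0.043/0.173 = 0.25.

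If exit depends only on baseline and the other covariates in the model, g = 0 and the shift is 0. Equal exits of the same kind in both arms cancel. Exits after week 4 do not touch the primary contrast.

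**The case against.** The strongest reply is that the bar is disclosed, applies equally to both arms, and is an ordinary way to keep a competing rehabilitation treatment out of the contrast. SOC only *may* include a recommendation for physical therapy, and a recommended course can often wait four weeks. The estimand is worded as a difference between treatment groups, which is correct as written. All of this stands. It shows that the bar is legitimate, but not that the unqualified label is right. The Discussion once speaks of medical SOC, but the article's own definition of SOC includes physical therapy.

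On follow-up, the Activity tracking sentence can be parsed another way: therapy is postponed until the study is completed or participation has ended, with leaving not offered as an option. PT/OT and staying in the study are incompatible on either parse, but the missing-data argument depends on the first. The full protocol, not shown here, may also still invite such people to the week-4 visit, and the point would then fall away. Controls also have a reason to stay, since after the week-4 assessments they "will have the opportunity to cross over immediately to participate in the EXP tango intervention".

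A reader might infer that the rule breaks intent-to-treat, or that every control must forgo PT/OT until week 16. The documents support neither. Participants are analysed as randomised; what may be lost is an outcome value, not group membership. The week-16 figure applies only to controls who take up the crossover.

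**Conclusion.** The point holds in a limited form and is minor. The mismatch between the comparator as labelled and as delivered follows from the text alone and needs no assumption. It concerns how widely the result can be generalised, not internal validity.

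The loss of week-4 TUG-Cog values rests on the natural reading of the Activity tracking sentence and on the full protocol not providing otherwise. Its size rests wholly on assumed inputs: 0.003 to 0.043 SD, or 0.025 to 0.25 of a standard error, with exits within the 20 losses per arm already planned. The number affected is probably small, because a participant must start PT/OT within four weeks of randomisation and prefer leaving to postponing. A reader might infer that the Aim 2 result is biased in a known direction, or materially; the documents give no basis for either the sign or a larger size.

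**What to change.** 1. **Name the comparator.** State in the control intervention section, the estimand and the conclusions that the comparator is SOC without PT/OT. This costs only wording.
2. **Separate the bar from outcome collection.** Keep the bar on PT/OT. Amend Activity tracking so that starting PT/OT is recorded as a deviation and does not end follow-up. Week-4 numbness and tingling and TUG-Cog are still measured unless consent is withdrawn, the participant is analysed as randomised, and PT/OT use is reported by arm.

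The second change needs a written amendment approved by the NIH and the IRB (Protocol amendments) in a trial enrolling since January 2025. Enrolment is expected to run to December 2028 (Trial status), so most participants could still benefit. No extra visits are needed; the week-4 visit and activity tracking already exist.

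The downside is slight dilution of the week-4 contrast. As a generous illustration, if 2–10% of controls used PT/OT and each gained as much as the full Tango target, the contrast would shrink by 0.02 × 0.56 = 0.011 to 0.10 × 0.56 = 0.056 SD. An as-randomised analysis is meant to include such use, and keeping the bar should hold the share down.

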###### Falls tracking:

Falling is defined as an unexpected loss of balance in which an individual comes to rest at a position lower than before the unexpected event (74). We elicit self-report of falls and loss of balance using the question “How many times have you fallen or felt like you lost your balance since we last saw you?” Responses are typed by the participant and reviewed for incidence of falls, incidence of loss of balance, and details offered about either incidence. During the 6-month follow-up period after intervention end, each participant will use the MyCap application to report falls weekly.

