## Methods

### Study Design

This is a multi-center, prospective randomized controlled study of superiority between an experimental intervention and usual care control arm. Eligible participants who provide informed consent will be randomly assigned to the Tango experimental (EXP) or the standard of care (SOC) control group (CON) in a 1:1 ratio. The study primary endpoints are changes from baseline to 4 weeks of intervention in the patient-reported outcome (PRO) of the sensations of numbness and/or tingling (Aim 1) and the quantitative outcome of dual task function during performance of a cognitive challenge simultaneously with a walking task (Aim 2). As an exploratory endpoint, we will assess the effect of Tango on the blood-based biomarkers that potentially mediate sensation and function as well as on cognitive load during a dual-task paradigm as measured by brain activity (i.e. high gamma) (Aim 3). Tables 1 & 2 present the data collection schedule for the EXP and CON groups, formatted per the Standard Protocol Items: Recommendations for Interventions Trials (SPIRIT) recommendations (43–45). Figure 1 illustrates the overall study design as a flow diagram. As detailed in Tables 1 & 2, outcomes are assessed at the following timepoints: repeated baseline (Baseline), primary endpoint (4 weeks of intervention or SOC), 8 weeks of intervention, 12 weeks (follow-up after a 4-week period of no structured intervention being offered), and weekly for 6 months following intervention end. Secondary outcome measures include clinical and biomechanical tests of function and patient-reported outcomes that complement the primary outcome measures in addition to falls incidence. Tertiary outcome measures, listed in Table 3, include within-session effects, satisfaction collected at session end, and surveys used to inform monitoring and shaping of interventions including Rating of Perceived Exertion - Physical (RPE-P; 6–20 scale), Rating of Perceived Exertion - Mental (RPE-M; 6–20 scale), and Intrinsic Motivation Inventory (IMI). To support beneficence, individuals randomized to the control arm will be given the option of participating in the experimental intervention after primary outcomes measurement.

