### Adverse event monitoring and reporting

Participants randomized to the CON group are asked to report adverse events at the beginning of each week during the SOC period using the MyCap application, a mobile application version of REDCap that participants install on their smart phone devices. Once these participants engage in the intervention (one-way crossover period) they report adverse events on the same schedule as the EXP group. Participants randomized to the EXP arm complete adverse event reporting each time we see them (2x per week) via REDCap. With respect to the adverse event of falls, participants are asked about the incidence of falls and loss of balance. Researchers review REDCap responses once per week for the CON participants within the SOC period and prior to the start of Tango lessons for participants engaging in the Tango intervention (EXP and crossed over CON). If an adverse event is reported, the PI is notified. Classification of the events as Serious or not occurs within 24 hours.

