## Figures and Tables

**Figure 1 F1:**
[figure not shown]
Flow chart of study design from screening through the follow-up (f/u) period with assessments indicated throughout. Postural control data will be taken at each Tango session in addition to all assessment periods. Each assessment timepoint may contain 1) clinical measures: PROs, dual-task function, and upper extremity function; 2) biomechanical measures: postural control and gait stability; and 3) exploratory measures: biomarker and EEG sampling. For more detailed information, refer to tables 1 & 2. Processing of data will happen after the conclusion of the follow-up period per participant. Analysis of the primary outcome measures will be conducted after all data has been collected.

**Table 1 T1:** SPIRIT report of intervention effect outcome measures for EXP group.

	Study Period						
	Enrollment		Allocation	Post-Allocation			
Timepoints	3 + months post-last taxane exposure	Baseline	0	EXP 4 weeks (Tango midpoint)	EXP 8 weeks (Tango end)	EXP 12 weeks (1-month follow up)	6-month follow up period, assessed weekly
ENROLLMENT:							
Eligibility screen	x						
Informed consent	x						
Allocation			x				
ASSESSMENTS:							
Adverse events (including falls)		x^†^		x	x	x	x
Neuropathy (primary outcome Aim 1)		x^†^		x	x	x	x
TUG-Cog (primary outcome Aim 2)		x		x	x	x	
CTCAE		x^†^		x	x	x	
Pain		x^†^		x	x	x	
Fatigue		x^†^		x	x	x	
GAD-2		x		x	x	x	
PHQ-2		x		x	x	x	
SF-36		x		x	x	x	
Satisfaction with intervention				x	x		
Activity outside of study tracking		x^†^		x	x	x	x
Intrinsic motivation				x	x		
Postural control during silence (QEC)		x^†^		x	x	x	
Postural control during music listening (QECm)		x^†^		x	x	x	
TUG		x		x	x	x	
TNSr+		x		x	x	x	
MiniBEST		x			x		
6mwt (EMG, IMUs)		x			x		
Upper extremity function		x		x	x	x	
Goal attainment (COPM)		x			x	x	
Blood-based biomarkers		x			x		
Cognitive load (EEG)		x		x	x	x	

† indicates a measure was repeated 3 times

**Table 2 T2:** SPIRIT report of intervention effect outcome measures for CON group.

	Study Period							
	Enrollment		Allocation	Post-Allocation				
Timepoints	3 + months post-last taxane exposure	Baseline	0	CON 4 weeks (post-SOC)	CON 8 weeks (Tango midpoint)	CON 12 weeks (Tango end)	CON 16 weeks (1-month follow up)	6-month follow-up period, assessed weekly
ENROLLMENT:								
Eligibility screen	x							
Informed consent	x							
Allocation			x					
ASSESSMENTS:								
Adverse events (including falls)		x^†^		x	x	x	x	x

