Neuropathy (primary outcome Aim 1)		x^†^		x	x	x	x	x
TUG-Cog (primary outcome Aim 2)		x		x	x	x	x	
CTCAE		x^†^		x	x	x	x	
Pain		x^†^		x	x	x	x	
Fatigue		x^†^		x	x	x	x	
GAD-2		x		x	x	x	x	
PHQ-2		x		x	x	x	x	
SF-36		x		x	x	x	x	
Satisfaction with intervention					x	x		
Activity outside of study tracking		x^†^		x	x	x	x	x
Intrinsic motivation					x	x		
Postural control during silence (QEC)		x^†^		x	x	x	x	
Postural control during music listening (QECm)		x^†^		x	x	x	x	
TUG		x		x	x	x	x	
TNSr+		x		x	x	x	x	
MiniBEST		x		x		x		
6mwt (EMG, IMUs)		x		x		x		
Upper extremity function		x		x	x	x	x	
Goal attainment (COPM)		x		x	x	x	x	
Blood-based biomarkers		x		x				
Cognitive load (EEG)		x		x	x	x	x	

† indicates a measure was repeated 3 times

**Table 3 T3:** SPIRIT report of within-session assessments. EMA refers to “Ecological Momentary Assessment”

Session Type	Baseline	Tango Intervetion		SOC (remote in MyCap app)
Timepoints	Before session start (Beg)	Before session start (Beg)	After completing session (End)	Weekly
ASSESSMENTS:				
Adverse events	x^a^	x^a^		
Neuropathy retrospective	x^a^	x^a^	x^b^	x^a^
PRO-CTCAE retrospective	x^a^	x^a^		x^a^
Pain retrospective (24 hours)	x	x		
Fatigue retrospective (24 hours)	x	x		
Neuropathy EMA	x	x	x	
CTCAE EMA	x	x	x	
Pain EMA	x	x	x	
Fatigue EMA	x	x	x	
Postural control during silence (QEC)	x	x		
Postural control during music listening (QECm)	x	x		
Activity outside of study tracking	x	x		x^a^
Satisfaction with session activity as neuropathy treatment			x	
Intrinsic motivation			x^c^	
COLLECTED TO FACILITATE TRIAL MONITORING AND INTERVENTION SHAPING:				
Rating of perceived physical exertion (RPE-P)			x^b^	
Rating of perceived mental exertion (RPE-M)			x^b^	

a Recall period = during the last week, since we last saw you, OR since you last answered these questions (whichever is the shortest time period)

b Recall period = during the activity just performed

c Queried every 2 weeks

**Table 4: T4:** EEG conditions

Condition	Description
Seated, eyes open	Resting data collected while seated. Participants will be instructed to watch a fixation point on a screen in front of them.
Quiet standing, eyes open	Participants will be instructed to stand with their eyes open while viewing a fixation point on a screen in front of them.
Quiet standing, eyes closed	Participants will be instructed to stand with their eyes closed.

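### Falls and felt loss of balance share one count tied to the last visit, so falls incidence cannot be reliably isolated and weekly app reports may overlap

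*Protocol article*

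**What the plan says.** The Falls tracking section first gives a definition: "Falling is defined as an unexpected loss of balance in which an individual comes to rest at a position lower than before" the event. It then elicits both falls and felt loss of balance with a single item: "How many times have you fallen or felt like you lost your balance since we last saw you". The handling of the answers follows: "Responses are typed by the participant and reviewed for incidence of falls, incidence of loss of balance, and details offered about either incidence". For the later period it adds: "During the 6-month follow-up period after intervention end, each participant will use the MyCap application to report falls weekly".

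Falls have two roles. Study Design lists, among the secondary outcomes, "patient-reported outcomes that complement the primary outcome measures in addition to falls incidence". Falls are also safety data: the schedules in Tables 1 and 2 place them in the row "Adverse events (including falls", and Adverse event monitoring and reporting says "participants are asked about the incidence of falls and loss of balance".

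A second recall window appears in footnote a of Table 3. It takes the shortest of three periods: the last week, or "since we last saw you, OR since you last answered these questions (whichever is the shortest time period". The footnote marks adverse events at baseline and at Tango sessions. In the weekly standard-of-care column it marks some items, but the adverse-events cell appears blank in the text at hand. Table 3 has no column for the 6-month follow-up.

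**The concern.** There are two problems in one item.

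The first is what is counted. The item asks for one number covering two kinds of event, but the plan intends to report two incidences. Participants are enrolled because their postural control lies outside normative values (Eligibility criteria), so felt loss of balance without a fall is to be expected in this population. If such episodes enter the falls count, or falls are lost among them, the secondary outcome no longer measures the event the protocol defines.

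The second is the time window. Recall back to the last visit works when participants are seen each time they answer. It does not suit someone who answers weekly by app without being seen, because successive answers can then cover the same weeks. This matters most in the randomised 4 weeks, when the arms report differently: Tango participants answer twice a week in person, and control participants answer weekly by phone.

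**Working it through.** The protocol states no falls rate or falls-specific power calculation, so there is no figure to reproduce. The check compares the relevant sections and then bounds the possible overlap.

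**Step 1: what one count can show.** Let F be falls as defined and B be losses of balance without a fall. The item returns N = F + B. A bare answer of N = 3 fits F = 0, 1, 2 or 3, which is four different falls counts. More information must come from typed detail or from a query. The section on the Aim 1 sensation outcome provides for going back to participants about incomplete or unclear answers, but only where the reviewer sees a need. No rule is given for a bare count.

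**Step 2: which window applies where.**

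| Report | Mode and frequency | Footnote a |
|---|---|---|
| Tango sessions | in person, twice weekly | marked |
| Control arm, standard-of-care weeks | app, weekly | adverse-events cell appears blank |
| 6-month follow-up | app, weekly | no column in Table 3 |

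The footnote is therefore printed where the visit-based wording does least harm, and is not shown against falls where that wording fits worst.

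**Step 3: bounds on repeat counting.** Assume K weekly app reports, no in-person contact between them, the quoted wording in the app and taken literally, events spread evenly over the weeks, and all answers summed. An event in week k is then reported K − k + 1 times, with mean (K + 1)/2.

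- Standard-of-care period, K = 4: (4 + 3 + 2 + 1)/4 = 10/4 = 2.5.
- Follow-up, K of about 26 (6 months of weekly reports): (26 + 1)/2 = 13.5, ranging from 1 to 26 by week of the event.
- Footnote a applied: windows do not overlap, so the factor is 1 in both periods.

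**Step 4: contrast between arms in the randomised 4 weeks.** Tango participants are seen at each report, so the literal window resets and the factor is 1. With equal true event rates, the apparent Tango-to-control rate ratio would be 1/2.5 = 0.4 under the literal reading and 1/1 = 1.0 under footnote a.

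**The case against.** Read quickly, the item suggests two stronger claims: that falls cannot be separated from near-falls at all, and that the trial will count events repeatedly. The documents support neither.

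On separation, the sentence after the item says the typed answers are examined for each kind of event. Reviewers may ask for clarification, and the secondary-outcomes section applies the same collection procedure to the other self-report surveys. Adverse event reports are reviewed weekly in the standard-of-care period and before each Tango lesson. Post-trial care has staff monitoring the 6-month responses. A bare number could be resolved through any of these routes.

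On repeat counting, the article does not say that the quoted item is the one used in MyCap. The sentence about the app refers to falls only. Recall to the last visit is also one of the three options in footnote a, so Falls tracking may be quoting the in-person version. The app form is not shown, and an article condenses such material. The larger figure also concerns follow-up after the randomised comparison has ended, when control participants may already have crossed over to Tango.

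A reader might further infer that the answers are sorted by staff who know the arm. The article does not state their blinding status. The only blinded role it describes is the TUG and TUG-Cog tester, and review schedules differ by arm, so the question is open.

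These points remove the absolute claims. They do not remove the weakness of the item: clarification is discretionary, the share of answers without detail is unknown, and the two recall windows are not reconciled for remote reports.

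**Conclusion.** The point holds in a limited form. As worded, the item does not allow falls to be reliably separated from felt loss of balance, because the split rests on volunteered detail or an optional query. How many records this affects cannot be computed, since the article gives neither event rates nor the share of bare-number answers.

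The window problem is conditional. Inflation runs from none, if footnote a governs every app report, to the worst-case averages in the working, which need every assumption listed there to hold together. These are bounds and not predictions. The possible difference between arms in the first 4 weeks carries the same conditions.

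One secondary and safety outcome is affected. The primary outcomes, the primary estimand and the sample size are not. The change should be made, but the trial's main conclusions do not depend on it.

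**What to change.** Replace the single item with two numeric fields: (a) falls, with the protocol's definition shown to the participant, and (b) losses of balance that did not end in a fall. Use one recall phrase in every REDCap and MyCap report, consistent with footnote a: the past week or the time since the previous answer, whichever is shorter. Show that window in Table 3 for adverse events in the standard-of-care column and for the 6-month follow-up. Analyse (a) as falls incidence, and flag records collected under the old wording so that they can be examined separately.

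The cost is a form change made by amendment, which under Protocol amendments needs NIH and IRB approval, and a set of early records whose wording differs. Enrolment opened in January 2025 and is expected to run to December 2028, so an early change keeps that set small. The added burden on participants is one extra number per report.
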